## **B. Evaluation Methods**

### ***1) Primary Efficacy Endpoint***

- The mean proportion of unscheduled hospitalizations in the intervention and control groups will be compared.

### ***2) Secondary Efficacy Endpoint***

- For each item in Domains 1 through 5, the means of continuous variables of the intervention and control groups will be compared. Additionally, the proportions of dichotomous variables of the intervention and control groups will be compared.
- Post-enrollment duration of survival in the intervention and control groups will be compared using the Kaplan-Meier curve.

## **C. Evaluation Interpretation**

### ***1) Primary Efficacy Endpoint***

- When the means of the continuous variables in the intervention group are 20% less than the means in the control group, it will imply that the HBMC intervention effectively reduced unplanned hospitalizations within 6 months of provision.

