|                              | 
2. Efficacy Endpoints
 
 
- Primary endpoint: The number of unscheduled hospitalizations within 6 months of study enrollment.
 
* Unscheduled hospitalization: This includes hospitalization at a respective participating institution for acute treatments (excluding scheduled hospitalizations for anti-cancer treatments, operations, and procedures), hospitalization at medical institutions other than the participating institutions, or hospitalization of 4 weeks or less at a nursing hospital.
 
- Secondary endpoint
 
 
n Patient: Medical service use (e.g., hospitalization and ER visit), critical care use (e.g., ICU admission and ventilator support), use of end-of-life medical services (e.g., ICU admission one month before death and ventilator support), satisfaction with the services, quality of life (ESAS and EQ5D), affective disorders (PHQ9), and preparation of advance directives.
 
n Guardian: Satisfaction with the services, quality of life (EQ5D), burden of care (CRA-K), affective disorders (PHQ9), and care competency.
 
n Costs: Medical expenses and care costs
                                                                                                                                                                                                                                                                                                                                                                                                                                                                                                                                                                                                                                                                                                                                                                                                                                                                                                                                                                                                     |

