| Statistical Analysis         | 
The HBMC intervention group, control group, and each participating institution will be set as analysis groups for the statistical analysis of the outcome variables.
 
The analysis groups of the participants are based on the group assignment according to the initial intention-to-treat (ITT) that relies solely on the intervention of the original assignment to estimate the effectiveness in the intervention group conservatively. In the case of withdrawal of consent or dropout during follow-up, data collected till the time of withdrawal or dropout will be used. A comparative analysis of the dropout rate between the two groups will be performed and reported.
 
 
- Descriptive analysis of underlying characteristics
 
 
Continuous variables: mean (standard deviation) and median (IQR)
 
Dichotomous variables: frequency (%)
 
 
- Analysis of between-group differences
 
 
An analysis will be performed using a regression model while considering that participants, the observation units, were clustered into six participating institutions to evaluate the effects of the HBMC intervention and correcting for the differences in the baseline characteristics between the groups.
 
Dichotomous variable (primary endpoint): A generalized estimation equation (GEE) will be used to analyze the clusters of patients in participating institutions, and the effects of the HBMC intervention will be evaluated using a logistic regression model based on the logit link function.
 
Continuous variables: The effects of the HBMC intervention will be evaluated using a mixed model to consider the patient clusters in the participating institutions.
 
Count data: A GEE will be used to consider the patient clusters in the participating institutions, and the effects of the HBMC intervention will be evaluated using a regression model that appropriately uses Poisson and negative binomial as random components according to the distribution of variables using the logit link function as the link function.
 |

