## 12. Efficacy Endpoint Evaluation Criteria, Methods, and Interpretation

### A. Evaluation Criteria

#### *1) Primary Efficacy Endpoint*

- The proportion of patients with unscheduled hospitalization within 6 months of study enrollment
- Definition of an unscheduled hospitalization: hospitalization at a respective participating institution for acute treatments (excluding scheduled hospitalizations for anti-cancer treatments, operations, and procedures), hospitalization at other medical institutions other than the participating institutions, or **hospitalization of 4 weeks or less at a nursing hospital**

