#### *2) Secondary Efficacy Endpoint*

- Domain 1: The secondary endpoints related to patients' use of medical services and critical care are described below.
  - Number of unscheduled hospitalizations within 6 months of study enrollment (continuous or count variable)
  - Length of hospitalization (total length of hospitalization; continuous variable)
  - History of hospitalization (dichotomous variable)
  - Number of ER visits (continuous variable)
  - Length of ICU hospitalization (total length of hospitalization; continuous variable)
- Domain 2: The secondary endpoints related to patients' quality of life and their satisfaction with the service are described below.
  - Patient's quality of life (EQ-5D; continuous variable)
  - Patient's degree of symptom control (ESAS; continuous variable)
  - Patient's emotional status (PHQ-9; continuous variable)

- Patient's satisfaction with the service (continuous variable)
  
- Domain 3: The secondary endpoints related to the patient's death and preparation of advanced directives are described below.
  - Survival after enrollment (days; continuous variable)
  - Length of ICU hospitalization within 1 month of the patient's death (total length of hospitalization; continuous variable)
  - History of anti-cancer treatment within 1 month of the patient's death (dichotomous variable)
  - Duration of ventilator support within 1 month of the patient's death (total number of days; continuous variable)
  - Preparation of advance directives or physician orders for life-sustaining treatment (dichotomous variable)
  
- Domain 4: The secondary endpoints related to guardians' quality of life and their satisfaction with the service are described below.
  - Guardian's quality of life (EQ-5D; continuous variable)
  - Guardian's emotional status (PHQ-9; continuous variable)
  - Guardian's burden of care (CRA\_K; continuous variable)
  - Guardian's care competency (continuous variable)
  - Guardian's satisfaction with the service (continuous variable)
  
- Domain 5: The secondary endpoints related to medical expenses are described below.
  - Direct medical expenses (continuous variable; KRW)
  - Indirect medical expenses (continuous variable; KRW)

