### ***2) Secondary Efficacy Endpoint***

- When the means of the continuous variables in the intervention and control groups differ at a significance level of 0.05 or less, it will imply that the HBMC intervention was effective for the secondary endpoint.

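### The primary success rule is a bare 20% threshold that does not fit the binary endpoint and is not tied to the planned test; separately, the synopsis and Section 12 name different primary endpoints

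*Protocol*

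**What the plan says.** **Success rule.** Section 12.C.1 is the only place that states which primary result shows that the programme works. Its condition is "When the means of the continuous variables in the intervention group are 20% less than the means in the control group". No p-value, confidence limit or model is mentioned. Section 12.C.2, directly below, does set a level for the secondary endpoints: "When the means of the continuous variables in the intervention and control groups differ at a significance level of 0.05 or less".

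**Planned inference.** Section 6 and the sample-size row of the Overview plan a logistic model fitted by GEE, with 80% power at a significance level of 0.05. The Statistical Analysis row of the Overview treats the primary endpoint as dichotomous and says "the effects of the HBMC intervention will be evaluated using a logistic regression model based on the logit link function". Section 14.A gives a 20% decrease as the hypothesis.

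**Primary endpoint.** The Efficacy Assessment row of the Overview has "Primary endpoint: The number of unscheduled hospitalizations within 6 months of study enrollment". Section 12.A.1 has "The proportion of patients with unscheduled hospitalization within 6 months of study enrollment". Section 12.A.2 then lists among the secondary endpoints "Number of unscheduled hospitalizations within 6 months of study enrollment (continuous or count variable)". Section 12.B.1 says "The mean proportion of unscheduled hospitalizations in the intervention and control groups will be compared".

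**The concern.** There are two defects, and neither causes the other.

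First, the rule in 12.C.1 is a threshold on a point estimate. It refers to means of continuous variables, which does not describe a yes/no outcome per patient, and it is not linked to the test that the trial was sized for. A result could therefore pass the threshold without being significant, or be significant with a reduction below 20%, and the protocol does not say which criterion decides. If the threshold decides alone, nothing in it limits the chance of a false claim of benefit.

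Second, the protocol names two different primary endpoints. The Overview assigns different models to binary and count outcomes, so the choice changes the primary analysis and could be disputed once results are known.

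**Working it through.** **Inputs from the protocol (Section 6 and its tables).** Three hospitals and 198 patients per arm, so m = 66 per hospital; ICC 0.015; level 0.05, taken as two-sided because sidedness is not stated; effect size 0.2; event counts 40 and 20 of 198 (20.2% and 10.1%), used for the ICC. **Not given:** the control rate behind the power calculation. Rates from 10% to 70% are therefore an assumption.

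**Step 1: reproduce the stated power.** Design effect = 1 + (66 − 1) × 0.015 = 1.975. Effective n per arm = 198 / 1.975 = 100.25.

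Power = Φ{[d√n − 1.96√(2p̄(1 − p̄))] / √(p₁(1 − p₁) + p₂(1 − p₂))}.

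Assuming 50% vs 30%: [0.20 × 10.01 − 1.96 × 0.693] / 0.678 = 0.950, so power = 0.829. The protocol states 0.83007. With 57 per hospital the design effect is 1.84, effective n is 171 / 1.84 = 92.9 and power is 0.800, against the stated 78.8%.

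Other readings at 66 per hospital:
- relative 20%, 50% vs 40%: 0.29
- relative 20%, 20% vs 16%: 0.11
- the protocol's own counts, 20.2% vs 10.1%: 0.51
- relative 20% comes close to 0.83 only near a control rate of 86% (86% vs 68.8%: 0.835), which nothing in the protocol suggests.

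The power table therefore points to 20 absolute points. The wording of 12.C.1, 20% less than the control mean, reads more naturally as relative.

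**Step 2: apply 12.C.1 alone, with no true effect.** Let both arms have true rate p.

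- Relative reading: success if p̂_T ≤ 0.8 p̂_C. By normal approximation, probability = Φ(−0.2p / √[1.64 p(1 − p) / 100.25]). At p = 0.20: 0.040 / 0.0512 = 0.782, giving 21.7%.
- Absolute reading: success if p̂_C − p̂_T ≥ 0.20. Probability = Φ(−0.20 / √[2p(1 − p) / 100.25]). At p = 0.50, the worst case: 0.20 / 0.0706 = 2.83, giving 0.23%.

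Beta-binomial simulation (at least 200,000 trials per rate, three hospitals of 66 per arm) agrees:

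| True rate in both arms | Relative, simulated | Relative, approximation | Absolute, approximation |
|---|---|---|---|
| 10% | 31% | 30.1% | <0.01% |
| 20% | 22% | 21.7% | 0.02% |
| 30% | 15–16% | 15.3% | 0.10% |
| 40% | 10% | 10.1% | 0.19% |
| 50% | 6% | 5.9% | 0.23% |
| 60% | 2.8% | 2.8% | 0.19% |
| 70% | 0.9% | 0.8% | 0.10% |

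For comparison, the favourable side of a valid two-sided 0.05 test is 2.5%. With 57 per hospital the relative figures for rates of 10% to 50% are about 32% down to 7%.

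**Step 3: check the replacement rule.** With no true effect and rates of 10% to 50%, a hospital-level t test on 4 degrees of freedom gives a false claim of benefit 2.3% to 2.6% of the time. An uncorrected sandwich-type z test with three hospitals per arm gives about 9%. Tying success to the GEE is therefore not enough without a small-sample correction.

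**The case against.** The strongest reply is that 12.C.1 should not be read in isolation. The protocol plans a logistic GEE at 0.05, and Section 14.A repeats the same 20% as the hypothesis. The sentence may only restate that effect, or set a threshold on top of the test. If both a valid test (the 4-df t test above) and a relative 20% reduction were required, false claims would occur 1.7% to 2.5% of the time. This stands in part: the protocol does plan a test, and the error rates above apply only if 12.C.1 is used alone. What it does not answer is that 12.C.1 neither mentions the test nor says that both are required, although 12.C.2 names a level.

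The endpoint conflict can also be overstated. Only the Efficacy Assessment row of the Overview names the count as primary. Section 12.A and the primary analysis model point to the binary endpoint, and so does the sample size, although its text loosely speaks of a 20% difference in number. The intended endpoint is clear enough, but the contradiction remains.

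Stronger readings that a reader might infer, and that the documents do not support:
- That the trial has a 6% to 31% false-positive rate. That range needs the relative reading, 12.C.1 used alone, and true rates of 10% to 50%.
- That the count/proportion conflict produces this error rate. It contributes nothing to it; the figures come from the missing link to a test.
- That the rule has poor power because it is met only about half the time when the true effect is exactly 20%. That is true of almost any point-estimate threshold set at the true effect.
- That 12.C.2 would count harm as benefit. Its wording has no direction, but the hypotheses in the Overview do.

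**Conclusion.** Both defects hold as written. The sole stated success rule for the primary endpoint does not fit a dichotomous outcome and is detached from the 0.05-level GEE, and the Overview contradicts Section 12.A on which endpoint is primary.

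The size of the first depends on a definition that the protocol does not give. With 12.C.1 used alone, ICC 0.015, 66 per hospital and three hospitals per arm, the chance of declaring an ineffective programme effective is about 22% on the relative reading at the 20% event rate in the protocol's ICC table. It is 31% to 6% for assumed rates of 10% to 50%, and under 3% at 60% or more. On the absolute reading it is about 0.2% or less.

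Confidence is high for the textual contradictions. The percentages are conditional on the assumptions listed. Because these statements fix the primary claim, they should be corrected in the protocol itself.

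**What to change.** 1. In both the Overview and Section 12, name the proportion of patients with at least one unscheduled hospitalisation within 6 months as the single primary endpoint, and keep the count as secondary.
2. Replace 12.C.1 with: the programme is judged effective if the primary logistic GEE, with a small-sample correction for six clusters, gives two-sided p < 0.05 in favour of HBMC. Report the effect estimate with its 95% confidence interval.
3. State that 20% is the planning effect, and whether it is absolute or relative, consistently in Sections 6, 12.C and 14.A and in the Overview.
4. As a minor wording change, require in 12.C.2 that the difference favour HBMC, in line with the directional hypotheses in the Overview.

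The cost is protocol wording only. No change to data collection or patient numbers follows from these edits.

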### ***2) Secondary Efficacy Endpoint***

- When the means of the continuous variables in the intervention and control groups differ at a significance level of 0.05 or less, it will imply that the HBMC intervention was effective for the secondary endpoint.

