| Hypotheses                                                     | 
 
1. Use of medical services, such as unscheduled hospitalizations and emergency room (ER) visits, will be significantly reduced among advanced cancer patients who receive home care education and participate in the HBMC intervention program as compared to the patients in the control group.
 
2. The quality of life (QoL) will be significantly higher, and the degree of symptom control will be significantly better among advanced cancer patients who receive home care education and participate in the HBMC intervention program than those in the control group.
 
3. The rate of establishing advance care planning will be significantly higher among advanced cancer patients who receive home care education and participate in the HBMC intervention program than those in the control group.
 
4. The mortality rate will be significantly lower among advanced cancer patients who receive home care education and participate in the HBMC intervention program than those in the control group.
 
 |
| Basis of the Study                                             | 
 
- The provision of home care environment-based intervention to patients with severe illnesses can significantly reduce readmission rates and improve survival rates compared to the provision of existing hospitalization and outpatient services (Malik et al., 2019).
 
- Symptom control is better when home-based palliative care services are provided to cancer patients (Gomes et al., 2013).
 
                                                                                                                                                                                                                                                                                                                                                                                                                                                                                                                                                                                                                               |

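### The secondary success rule in Section 12.C.2 states no direction, so read literally a significantly worse HBMC result would meet it; it also does not fit the dichotomous and survival endpoints

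*Protocol*

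**What the plan says.** Section 12.C.2 (Evaluation Interpretation, secondary endpoints) attaches a conclusion to a test result on the continuous endpoints. It is met if the two means "differ at a significance level of 0.05 or less, it will imply that the HBMC intervention was effective for the secondary endpoint". The only figure is the level of 0.05; sidedness is not stated.

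The methods text adds no direction. Section 12.B.2 says that "the means of continuous variables of the intervention and control groups will be compared" and that proportions will be compared for dichotomous items. Section 14.B.4 likewise describes a comparison between the two groups.

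Two other places do give a direction:
- Section 12.C.1, the primary rule, applies when "the means of the continuous variables in the intervention group are 20% less than the means in the control group". It is cited here only for its direction.
- The four hypotheses in the Overview expect less service use (ER visits included), more advance care planning and lower mortality under HBMC. On quality of life and symptoms they say: "The quality of life (QoL) will be significantly higher, and the degree of symptom control will be significantly better".

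Section 12.A.2 lists 21 secondary endpoints in five domains. Three are dichotomous: any hospitalization, anti-cancer treatment in the last month of life, and an advance directive or physician order. Survival is labelled continuous there, but Sections 12.B.2 and 14.B.4 assign it to Kaplan-Meier and Cox methods.

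**The concern.** The endpoints do not share a sign. Lower is better for ER visits or guardian burden; higher is better for EQ-5D, care competency or survival. A rule that asks only whether the means differ therefore cannot separate benefit from worsening, and no single implied sign would repair it.

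An unfavourable result is not far-fetched. Under Section 9.B the HBMC nurses contact patients every two weeks, the team may guide them to the ER, and patients are told when admission is needed. ER visits or expenses could rise for that reason. Under the literal rule a significant rise would count as evidence that HBMC worked.

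The rule also leaves gaps. It gives no criterion for a proportion or a hazard ratio, although the third hypothesis rests on a dichotomous endpoint and the fourth on mortality.

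**Working it through.** **1. Is a direction supplied anywhere?**

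| Endpoint group (Section 12.A.2) | Direction in an Overview hypothesis? | Direction in Section 12.C.2? |
|---|---|---|
| Service use, including ER visits | Yes, lower | No |
| Patient quality of life, symptom control | Yes, better | No |
| Advance directive or physician order | Yes, higher | No, and not a mean |
| Survival / mortality | Yes, lower mortality | No, and not analysed as a mean |
| Guardian quality of life, emotional status, burden, competency | No | No |
| Patient and guardian satisfaction | No | No |
| Direct and indirect expenses | No (the literature review in Section 2.B says HBMC lowers cost) | No |

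The intended direction can be recovered for the first four rows, but only by going outside the rule. For the last three rows no hypothesis helps.

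**2. How many endpoints does the rule reach?**

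Continuous or count endpoints by domain: 4 + 4 + 3 + 5 + 2 = 18. Dichotomous: 1 in Domain 1 and 2 in Domain 3, so 3. Total 21.

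From the 18, take out:
- patient and guardian satisfaction (2), which the table in Section 11.A marks as collected in the intervention group only at 3 and 6 months, so that no between-group test is possible;
- survival (1), which is not compared by means.

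This leaves 18 − 3 = 15.

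**3. Chance of a wrong-way result meeting the rule when HBMC has no effect**

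Assume valid two-sided tests at 0.05. Each endpoint then has 0.05 / 2 = 0.025 in the unfavourable tail.
- Expected number of significantly worse results: 15 × 0.025 = 0.375.
- At least one, if the tests were independent: 1 − 0.975^15 = 0.316, about 32%.

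Positive correlation lowers this, and admissions, hospital days, ICU days and direct expenses are likely to be correlated.

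**4. Chance of the wrong label when HBMC is truly worse on one endpoint**

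Assume a harm of d standard deviations, 198 patients per group (Section 6) and a normal approximation. The design effect is 1 (no clustering), or 1 + 65 × 0.015 = 1.975 from the protocol's cluster size of 66 and ICC of 0.015. With n = 198 / design effect and c = d / √(2/n):
- literal rule: Φ(c − 1.96) + Φ(−c − 1.96)
- directional rule: Φ(−c − 1.96)

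| d (assumed) | Literal, no clustering | Literal, design effect 1.975 | Directional (both cases) |
|---|---|---|---|
| 0.1 | 0.17 | 0.11 | below 0.004 |
| 0.2 | 0.51 | 0.29 | below 0.001 |
| 0.3 | 0.85 | 0.57 | below 0.001 |

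The values of d are illustrative; the protocol gives none for secondary endpoints. The approximation also ignores the small number of clusters (six).

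**The case against.** The best reply is that the protocol should be read as a whole. The Overview hypotheses pair significance with a direction for the outcomes that matter most, ER visits and quality of life among them. A sensible reader would take the word effective to mean different in the hypothesised direction. On that reading Section 12.C.2 is incomplete rather than contradictory. A worsening would still be visible in the reported group means, and further per-endpoint wording could sit in an analysis plan.

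Much of this stands. It shows what the investigators intended and limits the damage to wording. It does not clear the rule. Section 12.C.2 is a stated decision rule, not a detail left for later; it makes no reference to the hypotheses; and it is the only criterion for guardian outcomes and expenses.

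It is also fair to say that the 32% is the ordinary chance of some unfavourable significant result among 15 tests. A directional rule would not change that chance. It would change the label put on the result.

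**Conclusion.** The rule needs correcting. As written it lets a significantly worse result count as effectiveness, and it has no criterion for the three dichotomous endpoints or survival. It is a minor wording defect confined to the secondary endpoints: no estimate, p-value, sample size or primary conclusion depends on it. The 32% rests on 15 testable endpoints, no true effect, and valid, independent two-sided tests, and is an illustration only.

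A reader might infer more than the protocol supports:
- **That harm is meant to be reported as benefit.** The hypotheses show the opposite intention for most patient endpoints.
- **That the chance is 37%.** This is 1 − 0.975^18, which counts the two intervention-only satisfaction items and survival.
- **That testing at 3 and 6 months raises the figure generally.** The table in Section 11.A marks the 6-month EQ-5D, ESAS, PHQ-9 and guardian scales as intervention-only. The Overview and the text of Section 11.A suggest otherwise. Until these are reconciled, the remark cannot be made for the questionnaires.
- **That, with no safety assessment planned, worsening could be seen only in the secondary endpoints.** The primary endpoint would itself show more unscheduled hospitalizations, and its rule is directional.

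**What to change.** Reword Section 12.C.2 along these lines: *HBMC is judged effective on a secondary endpoint only if the cluster-adjusted effect (difference, odds ratio or hazard ratio, as suits the endpoint) is significant at the two-sided 0.05 level in the favourable direction listed for that endpoint. A significant effect in the opposite direction is reported as worsening.*

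Add a favourable-direction column to the list in Section 12.A.2. Take the direction from the Overview hypotheses where they give one, and have the investigators state it for the guardian, satisfaction and cost endpoints. A between-group criterion for satisfaction has meaning only if the control group also provides those data; otherwise mark those items as descriptive.

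The cost is one paragraph and one column, with no new data and no change to the tests. It should be done before between-group results are known, since a direction chosen afterwards could be challenged as driven by the results.

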### C. Secondary linkage data

Concerning patients in the intervention group who agree to provide secondary data linkage,

their National Health Insurance Service data will be accessed after more than 12 months of enrollment (Table 1). The relevant data will be used to investigate information on healthcare service use and direct medical cost up to 12 months after their enrollment. Data will be evaluated at 12 months to recalculate and utilize medical use and cost information at 3, 6, and 12 months. At 18 or more months after enrollment, all patients in the intervention study who provide consent for data sharing will be investigated for information on death, hospice use, healthcare service use before death, and advance care planning status. Table 1 shows the items to be investigated from the National Health Insurance Service data.

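### Section 12.C.2 lets each continuous secondary endpoint support its own claim of effectiveness at an unadjusted 0.05, with no gate, hierarchy or exploratory label

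*Protocol*

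**What the plan says.** Section 12.A.2 of the protocol lists the secondary endpoints in five domains and labels each by variable type. Examples are "Number of unscheduled hospitalizations within 6 months of study enrollment (continuous or count variable") in Domain 1, "Patient's satisfaction with the service (continuous variable") in Domain 2 and "Preparation of advance directives or physician orders for life-sustaining treatment (dichotomous variable") in Domain 3.

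Section 12.B.2 compares all of them: "For each item in Domains 1 through 5, the means of continuous variables of the intervention and control groups will be compared". Dichotomous items are compared as proportions. Section 14.B.4 repeats this.

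Section 12.C.2 then sets the rule for reading the results. Its subject is "When the means of the continuous variables in the intervention and control groups". If these "differ at a significance level of 0.05 or less, it will imply that the HBMC intervention was effective for the secondary endpoint". The rule is not conditional on the primary result. Nowhere does the protocol rank the secondary endpoints, divide alpha among them or call them exploratory.

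The Overview also words several of its hypotheses as significant differences, for example "The mortality rate will be significantly lower among advanced cancer patients who receive home care education" and who take part in the programme.

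On timing, the questionnaires are taken at enrollment, 3 and 6 months (section 11.A). Medical records are reviewed at 3, 6 and 12 months (section 11.B). Linked data run to 12 months, or to 18 months for some items (section 11.C).

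**The concern.** The protocol could have stayed silent on multiplicity and left it to the SAP. Instead it states an affirmative rule: a secondary endpoint that reaches 0.05 shows HBMC to be effective for that endpoint. An SAP that later added a gate or an adjustment would contradict section 12.C.2.

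A rule applied separately to 16 or more endpoints at full alpha will often produce at least one such statement when the programme does nothing. The rule also applies whether or not the primary endpoint succeeds. A chance finding on length of stay, quality of life, survival or cost could therefore be reported as an effect, under the protocol's own wording, beside a negative primary result.

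The missing analysis times add to this. Total length of hospitalization, number of ER visits, length of ICU stay and the two expense items carry no time in section 12.A.2, although data for them exist at more than one time.

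**Working it through.** The protocol states no familywise error figure, so there is none to reproduce.

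**Step 1. Count the endpoints the rule covers (section 12.A.2).**

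| Domain | Listed | Continuous or count | Dichotomous | Continuous, without satisfaction |
|---|---|---|---|---|
| 1 Service and critical care use | 5 | 4 | 1 | 4 |
| 2 Patient quality of life, satisfaction | 4 | 4 | 0 | 3 |
| 3 Death and advance directives | 5 | 3 | 2 | 3 |
| 4 Guardian | 5 | 5 | 0 | 4 |
| 5 Expenses | 2 | 2 | 0 | 2 |
| Total | 21 | 18 | 3 | 16 |

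Section 12.C.2 names continuous variables only, which gives 18. In the section 11.A schedule, patient and caregiver satisfaction carry only the intervention-group mark, so as scheduled they cannot be compared. That leaves 16.

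**Step 2. Set the assumptions.** HBMC has no effect on any endpoint. Each endpoint is tested once, and each test is exactly valid at two-sided 0.05. All pairs of test statistics share one correlation ρ. The protocol gives no ρ, so 0 to 0.8 is shown.

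**Step 3. Independent tests.** P(at least one) = 1 − (1 − α)^k.

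- Any difference, k = 16: 1 − 0.95^16 = 1 − 0.440 = 0.560.
- Any difference, k = 18: 1 − 0.95^18 = 1 − 0.397 = 0.603.
- Favourable differences only (α = 0.025 per test), k = 16: 1 − 0.975^16 = 1 − 0.667 = 0.333.
- Favourable differences only, k = 18: 1 − 0.975^18 = 0.366.

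**Step 4. Correlated tests.** Write Z_i = √ρ·U + √(1−ρ)·E_i, with U and the E_i independent standard normal. Then P(at least one) = 1 − ∫ φ(u) [P(|Z_i| < 1.96 given U = u)]^k du. For favourable differences only, use P(Z_i < 1.96 given U = u).

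| k | Counted as a claim | ρ = 0 | ρ = 0.3 | ρ = 0.5 | ρ = 0.8 |
|---|---|---|---|---|---|
| 16 | any difference | 56% | 48% | 37% | 21% |
| 16 | favourable only | 33% | 24% | 19% | 10% |
| 18 | any difference | 60% | 51% | 40% | 22% |
| 18 | favourable only | 37% | 26% | 20% | 11% |

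For a single test the error is 5% (any difference) or 2.5% (favourable only). The smallest 16-test values are thus about four times the single-test error: 21/5 ≈ 4.1 and 10.4/2.5 ≈ 4.1.

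If the correlation holds only within domains (blocks of 4, 3, 3, 4 and 2), at ρ = 0.5 the figures are about 50% for any difference and 29% for favourable differences only.

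**Step 5. Analysis times.** The figures above use one test per endpoint. Testing an endpoint at more than one time would raise them. By how much cannot be stated, because the protocol gives collection times and not a list of tests.

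**The case against.** The strongest reply is that these are labelled secondary endpoints. Section 12.C.2 speaks of effectiveness for the endpoint concerned, section 12.C.1 has its own rule for the primary, section 14.A states one hypothesis, on unplanned hospitalization, and the sample size rests on that one outcome. Reporting secondaries one by one without adjustment is common practice. That limits the consequence but does not remove it. Common practice is to report such results as supportive, whereas this rule attaches a conclusion of effectiveness to each.

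Several stronger readings are tempting, and the documents do not support them.

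- *All 21 endpoints fall under the rule.* They do not. The three dichotomous items, including advance directives, are compared, but the rule names continuous variables only.
- *The number of time points is open-ended.* It is finite: 3, 6, 12 and 18 months. Some items have a time or a single analysis already. The hospitalization count is set at 6 months, two continuous items are tied to the month before death, and survival is one analysis. As tabulated in section 11.A, the patient and caregiver scales have control-group data after baseline only at 3 months, although the text of 11.A and the Overview read differently for 6 months. Section 11.C says "Data will be evaluated at 12 months to recalculate and utilize medical use and cost information at 3, 6, and 12 months", but this describes deriving data and is worded for intervention-group patients. It does not set repeated group comparisons.
- *A false claim is likely, at about 43%.* That figure needs 21 two-sided tests and an equal correlation of 0.5 that no document gives. It is below one half, and it counts harmful differences as false claims.
- *The Overview hypotheses are co-equal.* They are numbered and not ranked, and nothing calls them co-equal.
- *The whole trial would be declared effective on a secondary.* Section 12.C.2 makes endpoint-specific statements only, and the Overview's aim of supporting dissemination is not tied to any secondary result.

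**Conclusion.** The point stands in a limited form. Section 12.C.2 fixes an unadjusted 0.05 rule under which each of 18 continuous secondary endpoints, or 16 as scheduled, can support its own statement that HBMC was effective. Nothing gates, ranks or qualifies these statements, and several endpoints have no named analysis time.

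If HBMC has no effect, the chance of at least one false statement among 16 single tests is about 56% down to 21% for any difference. Counting only favourable differences, it is 33% down to 10%. Both ranges run from correlation 0 to 0.8, which is assumed. The conclusion does not turn on 16 against 18 endpoints or on one correlation, since every case shown is at least about four times the error of a single test. The primary analysis is not affected. The rule should be changed.

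**What to change.** Replace the rule in section 12.C.2 with: *Secondary endpoints are supportive and are reported as between-group estimates with 95% confidence intervals and nominal p-values; the conclusion on effectiveness rests on the primary endpoint.* In section 12.A.2, name one analysis time for each secondary endpoint and mark the others as descriptive. Align the significance wording of the Overview hypotheses with this.

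This is a change of wording and needs no further patients or data. What is lost is the ability to present an isolated secondary p<0.05 as proof of effectiveness.

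If confirmatory secondary claims are wanted, name a few endpoints, each at one time, and test them with Holm's procedure only after the primary succeeds. That also requires rewriting section 12.C.1. Its present criterion is a 20% lower mean with no significance test, so there is no primary test result on which to gate.
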